**Trial registration:**

Patient enrolment in the trial started in January 2021 and is expected to finish at the end of 2022. The study can be found on ClinicalTrials.gov database with NCT05125913 identifier.

Registered on 18 November 2021 - Retrospectively registered.

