### Objectives

The objectives of this observational study are to determine:the feasibility of flow mediated dilation (FMD), bioimpedance spectroscopy (BIS) fluid assessment, lung ultrasound (LUS) and pulse wave velocity (PWV) measurement in CKD patients following COVID-19 and matched CKD control-patients without a history of previous SARS-CoV-2 infection;the long-term impact of the COVID-19 on markers of CV risk and ED in patients with CKD and KTx on a composite CV outcome (time to first non-fatal myocardial infarction, non-fatal stroke, hospitalization for heart failure or CV death) and on all-cause mortality;the long-term impact of the COVID-19 on markers of CV risk and ED in patients with CKD and KTx on a composite renal outcome: doubling of creatinine or a 40% decline in eGFR or dialysis initiation.

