### Study design

This observational cohort study will include CKD (stage 3 to 5), dialysis and KTx patients from dialysis unit’s auxiliary to Dr. C.I. Parhon University Hospital, Iasi, Romania, diagnosed with COVID-19 according to the interim guidelines of the WHO [28] using the reverse transcriptase polymerase chain reaction (RT-PCR) assay from nasal or throat swab. Patients from North-East of Romania with a documented history of SARS-CoV-2 will be recruited into the CARDIO SCARS IN CKD observational cohort study. All participants must have recovered from acute illness due to SARS-CoV-2 virus infection.

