#### Inclusion criteria

Age > 18 years;Patients with CKD stage 3–5, including dialysis or KTx with confirmed COVID-19, at minimum 2 weeks after the confirmed test;Age, sex and kidney disease (CKD stage 3–5, dialysis or KTx) matched patients without confirmed SARS-CoV-2 infection.

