### Screening and enrolment

All study procedures (as pointed in Table 1 and Fig. 2), including screening and enrolment, will be conducted by trained personnel with backgrounds in cardiology, nephrology, internal medicine and medical science. We will recruit participants from the investigators’ clinic patient panel at [name] Clinical Hospital of Iasi and dialysis units from Iasi. Investigators will also partner with other providers from nearby hospitals and/or dialysis centres for enrolment. We will approach participants during routine clinic visits. For retention, we will leverage the electronic medical record to track hospitalizations and scheduled clinic visits during the study period. All participants will first undergo a brief screening discussion, via telephone or in person, to determine eligibility and interest. Participants will be queried on their health history including the presence of other major medical illnesses, to ensure that no exclusion criteria are present. If eligible, participants will be invited to participate in a 1-hour baseline assessment, when each participant will undertake a detailed interview in order to summarize the patient datasheet, further included into the trial database. During the baseline assessment, informed consent will be presented by the study staff including a description and timing of the study procedures, potential risks and benefits of study involvement, rights to withdraw from the study, and details regarding protections against study risks. All participants will receive a copy of their signed informed consent form.

**Table 1 Tab1:** Study procedures flowchart

Procedures/Timepoint		Study interventions			
	Enrolment	Baseline	6 months	12 months	24 months

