Echocardiography	- according to the American Society of Echocardiography recommendations by an observer unaware of the LUS and bioimpedance results; - measurements: cardiac anatomy (e.g. volumes, geometry, mass) and function (e.g. left ventricular function, valvular function, right ventricular function, and pulmonary artery pressure); - in patients with adequate acoustic windows, both left ventricular global longitudinal strain (LVGLS) and right ventricular free wall strain (RVFWS) will be calculated.
LUS	- patient in the supine position; - measurements of the anterior and lateral chest on both sides of the chest, from the second to the fourth (on the right side to the fifth) intercostal spaces, at parasternal to mid-axillary lines; - B-lines will be recorded in each intercostal space and were defined as a hyperechoic, coherent US bundle at narrow basis going from the transducer to the limit of the screen; − B-lines starting from the pleural line can be either localized or scattered to the whole lung and be present as isolated or multiple artifacts; - the sum of B-lines produces a score reflecting the extent of lung water accumulation (0 being no detectable B-line).
BIS	- portable whole-body multi-frequency bioimpedance analysis device (BCM®Body Composition Monitor – Fresenius Medical Care D GmbH); - electrodes will be attached to the patient’s forearm and ipsilateral ankle, with the patient in a supine position; - measurements: body resistance and reactance to electrical currents of 50 discrete frequencies, ranging between 5 and 1000 kHz; - calculations: ECW, ICW and TBW, to determine the amount of fluid overload; - AFO is defined as the difference between the expected patient’s ECW under normal physiological conditions and the actual ECW, whereas RFO is defined as the absolute fluid overload AFO to ECW ratio.
Blood collection for biomarker evaluation	- whole blood will be collected in gel & clot activator tubes (minimum 3.5 mL tube) at each intervention visit for each patient; - serum will be collected by centrifugation and frozen in aliquots at −80 ° C until further analysis; - IL1, IL6, VCAM-1, endoglin, NO and ADMA in serum samples will analysed by specific enzyme linked immunosorbent assay (ELISA) kits on a Sunrise Basic Tecan microplate reader.

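### The control criterion can admit patients with past but unconfirmed COVID-19, whereas the Objectives describe controls with no previous infection

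*Protocol article*

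**What the plan says.** The protocol article describes the control group in two ways. The Inclusion criteria, which decide who is enrolled, ask for "matched patients without confirmed SARS-CoV-2 infection". The first item under Objectives, on the feasibility of the vascular, lung and fluid measurements, refers to "matched CKD control-patients without a history of previous SARS-CoV-2 infection". Study population describes a single non-COVID group of at least 125 patients, so the same controls serve every objective.

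Study design says that the COVID patients are diagnosed "using the reverse transcriptase polymerase chain reaction (RT-PCR) assay from nasal or throat swab". No other method of confirmation is named.

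The check on eligibility is described under Screening and enrolment: "All participants will first undergo a brief screening discussion, via telephone or in person, to determine eligibility and interest". Health history is queried at that point, and a detailed interview follows at baseline. The Exclusion criteria do not mention earlier suspected, antigen-diagnosed or clinically diagnosed COVID-19. Neither Table 1 nor Table 2 lists a swab or a SARS-CoV-2 antibody test. The laboratory work is "IL1, IL6, VCAM-1, endoglin, NO and ADMA in serum samples will analysed by specific enzyme linked immunosorbent assay (ELISA) kits". Serum is kept, however: "serum will be collected by centrifugation and frozen in aliquots at −80 ° C until further analysis". The limitations section does not mention unrecognised infection among controls.

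**The concern.** An unconfirmed infection is not the same as no infection. Under the Inclusion criteria as worded, three kinds of previously infected patient can qualify as controls: those diagnosed only by antigen test, those diagnosed only clinically, and those never tested. They would carry the exposure that the study sets out to assess.

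There was time for this to happen. The Background dates the pandemic declaration to March 2020, and the registration paragraph states: "Patient enrolment in the trial started in January 2021 and is expected to finish at the end of 2022". The article also treats mild disease as relevant. Its Background reports worse renal outcomes even after mild symptoms, and its Discussion cites myocardial injury after mild or asymptomatic forms.

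If COVID-19 has the harmful effect the study expects, previously infected controls move the non-COVID group's outcomes towards those of the COVID group. That affects mortality, the cardiovascular composite, the endothelial markers and the renal composite, and makes a finding of no difference harder to interpret.

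**Working it through.** **Inputs from the protocol article.** Mortality of 9% (non-COVID) and 22% (COVID), alpha 0.05 and power 80% (Sample size power calculation); n = 125 per group (Study population). The article does not say whether the test is one- or two-sided; two-sided is assumed.

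**Inputs not in the article (assumptions).** m is the share of controls with unrecognised past infection, shown at 10%, 20% and 30%. f is the fraction of the planned excess risk that those infections carry, shown at 1 (full) and 0.5 (half).

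**Formula.** Normal approximation for two proportions, pooled variance under the null, no continuity correction:

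power = Φ{ [d − 1.96·√(2·p̄(1−p̄)/n)] / √[(p0(1−p0) + p1(1−p1))/n] }, where d = p1 − p0 and p̄ = (p0 + p1)/2.

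**Step 1: the plan's own figure.** With p0 = 0.09, p1 = 0.22 and n = 125: d = 0.13 and p̄ = 0.155.
- Null term: 1.96 × √(2 × 0.155 × 0.845/125) = 1.96 × 0.04578 = 0.0897.
- Denominator: √((0.0819 + 0.1716)/125) = 0.0450.
- Power = Φ((0.13 − 0.0897)/0.0450) = Φ(0.894) = 81.4%.

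The stated 80% is therefore reproduced. The same formula needs 121 per group for 80%, so 125 leaves little reserve.

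**Step 2: dilution.** The control rate becomes 9% + f·m·13%, so the difference becomes 13 × (1 − f·m) points. For example, with m = 10% and f = 1 the control rate is 9 + 1.3 = 10.3% and the difference is 11.7 points.

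| m | Difference, full excess | Power | Difference, half excess | Power |
|---|---|---|---|---|
| 0 | 13.0 | 81.4% | 13.0 | 81.4% |
| 10% | 11.7 | 71.3% | 12.35 | 76.6% |
| 20% | 10.4 | 59.5% | 11.7 | 71.3% |
| 30% | 9.1 | 47.4% | 11.05 | 65.5% |

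A mean marker difference shrinks by the same factor, 1 − f·m. It shrinks by 1 − m only if unrecognised infections have the full effect.

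**Step 3: does any other described step close the gap?** The interview can pick up a known antigen-positive or clinically diagnosed episode, but the criterion as written does not make such an episode disqualifying. No interview can reveal an infection the patient never knew about, and no laboratory test for one is listed.

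**The case against.** The strongest reply is that the two passages barely conflict. The stricter wording belongs to the feasibility objective. The objectives on cardiovascular outcome, mortality and renal outcome name no never-infected comparator, and the opening of Methods speaks only of matched controls. Study design refers to COVID patients with a documented history, so 'history' and 'confirmed' might be meant as one clinical standard. RT-PCR is given as the way cases are diagnosed, not as the only evidence that counts against a control. Staff may well turn away an antigen-positive candidate under the full protocol.

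Part of this stands. The conflict is one of wording, and a sensible site could resolve it in the right direction. But there is only one non-COVID group, and the eligibility rule is what governs enrolment. Nothing in the article says that an infection shown by other means rules a control out.

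The objections to size stand in full. The article gives no value for m. Unrecognised infections are probably milder, and the article itself links both renal outcomes and flow-mediated dilation to severity, so the full-excess column is an upper bound. A reader might also infer that the share of such controls rises through recruitment. The article does not show that: cumulative infection rises, but access to testing may rise too.

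The objection to compulsory serology is also sound. Removing seropositive controls after enrolment disturbs the matching and could take the group below 125. Replacing them means new visits and blood draws. Spare serum and ethics cover for a further assay cannot be assumed.

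**Conclusion.** The control criterion is looser than the description of controls in the Objectives. As written, it allows previously infected patients into the non-COVID group. The possibility follows from the text. The direction, towards no difference, follows if COVID-19 is harmful. The size does not follow from the text: the fall from 81% power to 71%, 60% and 47% (full excess risk) or to 77%, 71% and 66% (half) at m = 10%, 20% and 30% is illustrative.

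Two stronger readings are not supported. One is that infected patients do enter the control group; the article shows only that they can. The other is that a null result would be uninterpretable; at a low m or a mild effect the loss is modest, for example 76.6% power at m = 10% with half the excess risk. The point concerns infection before baseline only. It justifies an inexpensive correction to one criterion and does not undermine the design.

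**What to change.** Align the control criterion in the Inclusion criteria with the Objectives. Suggested wording: matched patients with no positive RT-PCR or antigen test for SARS-CoV-2 and no clinical diagnosis of COVID-19 at any time before baseline, established from medical records and the screening interview. For controls already enrolled, make the same check from records and report how many would not have met the revised rule. Add unrecognised infection among controls to the stated limitations.

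This costs one changed criterion and one question in an interview that already takes place. The downside is that a few control candidates are lost. Silent, untested infections remain undetected.

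Optionally, where spare baseline serum and ethics approval allow, test the controls' stored samples for anti-nucleocapsid antibody. Spike antibody would be less useful because it also reflects vaccination, and vaccination status is listed only for the COVID arm under Clinical data. Repeat the contrasts without seropositive controls as a sensitivity analysis, adjusting for age, sex and kidney disease category because the matching is then broken. State that waning antibody and immunosuppression, the latter relevant to the transplant patients, leave some misclassification. The cost is one further ELISA on about 125 samples.

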#### Exclusion criteria

Prior diagnosis of pulmonary fibrosis, pneumectomy or massive pleural effusion;Active malignancies;Pregnancy;Active systemic infections (due to difficulties in the interpretation of nonspecific inflammation biomarkers in this type of patients);Congenital heart disease.

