### Study population

We aim to enrol 250 patients, divided into two groups with minimum 125 patients per group: COVID group and non-COVID group. Both groups will be monitored at 6, 12 and 24 months since the first procedure visit, defined as the baseline.

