**Enrolment**					
*Eligibility screen*	*X*				
*Contact information*	*X*				
*Informed consent*	*X*				

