**Assessments**					
*Clinical data*	*X*	*X*	*X*	*X*	*X*
*IL1, IL6, VCAM-1, endoglin, NO and ADMA*		*X*	*X*	*X*	*X*
*CV risk*			*X*	*X*	*X*
*Mortality rate*					*X*
*Renal outcome*			*X*	*X*	*X*
*ED*					*X*

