#### Clinical data

Personal data (age, sex, height); CV risk factors (smoking, alcohol use, weight, body mass index); comorbidities (diabetes, hypertension, coronary artery disease, heart failure etc); physical examination (blood pressure, heart rate, crackles, pedal edema etc); type of renal disease; renal function (urea, creatinine, proteinuria, etc); medication; inflammation evaluation: CRP; complete blood count will be collected.

For the dialysis population: dialysis vintage and for the transplantation population: dialysis vintage before transplantation; date of transplantation, type (living or cadaveric donor), mismatch number, type of induction therapy; type of chronic immunosuppression therapy, will be also collected. Supplementary, for the COVID arm, we will assess also the severity of the infection, administered treatment, use of oxygen therapy, vaccination status.

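### The infection exclusion that protects the inflammation markers at entry is not carried to the 6-, 12- and 24-month blood draws

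*Protocol article*

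**What the plan says.** - **Exclusion criteria** bar patients with "Active systemic infections (due to difficulties in the interpretation of nonspecific inflammation biomarkers in this type of patients". The bracketed reason concerns how a marker value is read, not patient safety or prognosis.
- **Screening and enrolment** says how exclusions are checked: "Participants will be queried on their health history including the presence of other major medical illnesses, to ensure that no exclusion criteria are present". This is part of a brief discussion held by telephone or in person. In Table 1 the row "Eligibility screen" is marked in the enrolment column only.
- **Study population** sets the visits: "Both groups will be monitored at 6, 12 and 24 months since the first procedure visit, defined as the baseline".
- **Table 1** marks blood collection and the panel "IL1, IL6, VCAM-1, endoglin, NO and ADMA" at baseline, 6, 12 and 24 months.
- **Table 2**, blood collection: "whole blood will be collected in gel & clot activator tubes (minimum 3.5 mL tube) at each intervention visit for each patient". No condition on infection status is attached.
- **Clinical data**, which Table 1 marks at enrolment and at all four visits, include a physical examination and "inflammation evaluation: CRP; complete blood count will be collected".
- **Outcome data** make the long-term impact of COVID-19 on markers of cardiovascular risk and endothelial dysfunction one of the primary outcomes.
- **Statistical analysis** does not mention infection occurring during follow-up.

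**The concern.** A reason that rests on reading a marker correctly holds for every sample of that marker. The plan acts on it once, at entry. The long-term question is answered by the later samples, and Table 1 marks the cardiovascular-risk assessment only at 6, 12 and 24 months. The cohort includes dialysis patients and transplant recipients on chronic immunosuppression, so some infections during 24 months of follow-up are foreseeable. Followed as written, the plan would draw IL1 and IL6 during such an infection and analyse the result as a long-term post-COVID value.

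Two things are at stake. Infections equally common in both groups add noise to the comparison. Infections more common in one group also add a between-group difference that reflects the current infection and not the lasting vascular or inflammatory state the study wants to describe.

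**Working it through.** The article gives no figure of its own on this point. Its only computed figure is the mortality sample size (9% vs 22%, 125 per group, alpha 0.05, 80% power). That reproduces on power, at 81.4% two-sided, and nothing below alters it.

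**Step 1: what is covered (from Table 1)**

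| Item | Enrolment | Baseline | 6 mo | 12 mo | 24 mo |
|---|---|---|---|---|---|
| Eligibility screen | X | | | | |
| IL1/IL6 panel and blood draw | | X | X | X | X |
| Clinical data (examination, CRP, blood count) | X | X | X | X | X |

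Scheduled samples at 250 patients: 250 × 4 = 1,000. Follow-up samples: 250 × 3 = 750, or 3/4, before deaths and dropout. Information bearing on infection is collected at each visit, but no rule says how to use it.

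**Step 2: how many samples might be affected**

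The share p of follow-up visits falling during an active infection is an assumption. Affected samples = 750p. Patients with at least one affected sample = 1 − (1 − p)³, assuming independent visits.

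| p | Affected samples | Patients with at least one |
|---|---|---|
| 1% | 7.5 | 3% |
| 3% | 22.5 | 9% |
| 5% | 37.5 | 14% |
| 10% | 75 | 27% |

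**Step 3: effect on precision, IL-6 only**

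All inputs are assumptions: infected share f of 3-8%, k-fold rise of 5-10, log-scale SD 0.8 (variance 0.64).

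- Added log variance = f(1 − f)(ln k)²
- Efficiency of a mean-based comparison = 0.64 / (0.64 + added variance)
- Efficiency of a rank test, relative to the same test on uncontaminated data = {(1 − f)² + f² + 2f(1 − f)·exp[−(ln k)²/(4 × 0.64)]}²

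| f | k | Added variance | Mean-based | Rank test |
|---|---|---|---|---|
| 3% | 5 | 0.0291 × 2.590 = 0.075 | 0.90 (0.895 unrounded) | 0.93 |
| 5% | 10 | 0.0475 × 5.302 = 0.252 | 0.72 | 0.84 |
| 8% | 10 | 0.0736 × 5.302 = 0.390 | 0.62 | 0.76 |

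The Statistical analysis section names both kinds of method (ANOVA and regression after log conversion; Kruskal-Wallis), so both columns are relevant.

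**Step 4: effect on the group difference**

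Shift in the log-mean difference = (f₁ − f₀) ln k.

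- Equal rates: 0.
- 8% vs 3%, k = 10: 0.05 × 2.303 = 0.115, about 12% in geometric mean.
- 8% vs 3%, k = 5: 0.05 × 1.609 = 0.080, about 8%.

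The larger shift is about 0.12 of the SD of the contaminated data. The standard error of a difference at 125 per group is √(2/125) = 0.126 SD, so even this assumed imbalance moves the estimate by slightly less than one standard error.

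**The case against.** The strongest reply is that this is no contradiction. An exclusion criterion governs entry and normally has no counterpart at follow-up, and a journal article may leave deferral rules, visit windows and sample flags to a fuller document. The first part stands: the rationale has not been extended, and no two statements conflict. The second stands only in part. Table 2 does state measurement conditions at visit level, such as withholding vasoactive drugs before flow-mediated dilation, rest periods, and the choice of arm when a fistula is present. For blood it fixes the draw "at each intervention visit for each patient", with no condition.

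Several stronger readings are tempting and are not supported:

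- **That infection makes the markers uninterpretable.** The article speaks of difficulties in interpreting them.
- **That nothing at follow-up could reveal an infection.** Examination, CRP and blood count are collected at every visit, and hospitalizations are tracked through the electronic record. What is absent is a rule for using this information.
- **That the whole panel, flow-mediated dilation and lung ultrasound fall under the same reason.** It names nonspecific inflammation markers, which plainly covers IL1, IL6 and CRP. Extending it to VCAM-1, endoglin, NO, ADMA or the imaging measures is inference.
- **That baseline is securely protected and follow-up is not.** The entry check is a history query at screening and is not tied to the baseline draw, so the contrast is weaker than it looks.
- **That the group comparison is biased.** This needs unequal infection rates, on which the document gives no figure.

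A further objection concerns the remedy, and it stands. Infection after baseline may itself follow from COVID-19 or its treatment. Dropping infected samples from the main comparison would condition on an event that comes after the exposure. Using a CRP cut-off to decide would also selectively remove patients with high inflammation, possibly including the persistent inflammation under study.

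**Conclusion.** The point holds as a cheap improvement, not as an error. The plan gives a measurement reason for keeping active systemic infection away from its inflammation markers, then schedules IL1 and IL6 unconditionally at three of four visits for a primary outcome about long-term effects.

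The size of the gain is unknown. The efficiency range of about 0.62-0.90 applies to IL-6 alone and to mean-based methods, and it rests wholly on the assumed prevalence, fold-rise and SD. Rank tests lose less (0.76-0.93 under the same assumptions). A shift between groups requires an imbalance that the document neither states nor suggests. The mortality sample size is unaffected.

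**What to change.** Add to the procedures for the 6-, 12- and 24-month visits, identically in both groups:

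1. Record whether active systemic infection is clinically evident, from the examination and history already collected and not from a CRP cut-off alone.
2. If it is, postpone the biomarker draw until the infection has resolved, within a stated window around the visit.
3. If that is not possible, take the sample and flag it.
4. Keep all samples, flagged ones included, in the main marker comparison, and prespecify a sensitivity analysis without the flagged samples.
5. Collect outcome events on the original schedule whether or not the draw is postponed.

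The cost is a short addition to the visit procedures, one item on the visit form and a few postponed draws. Infection status not recorded at the draw may be hard to reconstruct later, so the item should be in place before further follow-up samples are taken.
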